### Intervention

Participants randomised to the intervention group will receive access to a web-based information tool and nurse-delivered telephone support for the duration of the study.

### Development of web-based information tool

#### Development of content

The web-based information tool was developed by the Health Behaviour Research Group, University of Newcastle, Australia, in collaboration with the Department of Haematology, Royal North Shore Hospital, Australia, and a multi-disciplinary expert advisory group. The content of the intervention web program was developed using patient information resources from the Leukaemia Foundation Australia, the Cancer Council New South Wales and Macmillan Cancer Support (UK). Permission from these organisations was obtained prior to adaptation of materials. All information sources are clearly acknowledged in the web-based information tool. Two expert advisory groups were convened to review and update content and ensure acceptability and consensus among clinical haematological cancer professionals. Expert advisory groups comprised multidisciplinary health care providers, including haematologists, nurses, clinical psychologists, dietitians, infectious disease experts and palliative care coordinators, as well as members of key patient support organizations. The advisory groups were responsible for reviewing all intervention materials for accuracy, completeness, level of detail, and communication style. Feedback was then collated and discussed at the advisory group meetings until consensus was reached regarding the content. Revised versions of the content were then circulated to members for final review and feedback. The final version of the web-based tool includes information on a range of topics, including information about diagnosis, treatment options, what is involved in each treatment, side effects, self-management strategies, impact of cancer on day to day life, available support, complementary and alternative therapies (see Table 1).

**Table 1 Tab1:** **Web-based information tool content headings**

Domain	Content
1. Introduction	1.1 Introduction
2. My cancer and its causes	2.1a Acute myeloid leukaemia
	2.1b Acute lymphoblastic leukaemia
	2.1c Burkitt’s lymphoma
	2.1d Lymphoblastic lymphoma (B or T cell)
3. What are my treatment options?	3.1 Chemotherapy
	3.1.1 What does chemotherapy involve?
	3.1.1.1 What tests will I require before and during treatment?
	3.1.1.2 How is chemotherapy given?
	3.1.1.2.1 Cannula
	3.1.1.2.2 Central lines
	3.1.1.2.3 PICC lines
	3.1.1.2.4 Lumbar puncture
	3.1.1.3 How long does chemotherapy take?
	3.1.1.4 Where will I have chemotherapy?
	3.1.1.5 Who will be involved in my care?
	3.1.1.6 What are the safety precautions?
	3.1.1.7 How and when will I know if the chemotherapy has worked?
	3.1.2 What are possible side effects?
	3.1.2.1 Effects on the blood and immune system
	3.1.2.1.1 Avoiding infection
	3.1.2.2 Hair loss or scalp problems
	3.1.2.3 Loss of appetite, nausea or vomiting
	3.1.2.4 Constipation or diarrhoea
	3.1.2.5 Fatigue
	3.1.2.6 Itchy skin and other skin problems
	3.1.2.7 Mouth sores
	3.1.2.8 Infertility
	3.1.2.9 When to contact your doctor
	3.1.3 What happens after chemotherapy?
	3.1.3.1 What happens when I go home?
	3.1.3.2 What are the chances of the cancer coming back?
	3.1.3.3 When should I seek medical assistance?
	3.2 Bone marrow transplant
	3.2.1 What is bone marrow?
	3.2.2 What is a bone marrow transplant?
	3.2.3 Is a bone marrow transplant right for me?
	3.2.4 Types of bone marrow transplants
	3.3 Palliative care
	3.3.1 What does palliative care involve?
	3.3.1.1 How long does palliative care take?
	3.3.1.2 Where would I have palliative care?
	3.3.1.3 Who will be involved in my care?
	3.3.1.4 Can my carer access respite care?
	3.3.2 Symptom management
	3.4 No treatment
	3.5 Clinical trials
	3.5.1 What is a clinical trial?
	3.6 Getting a second opinion
4. Complementary and alternative medicine (CAM)	4.1 What is CAM?
	4.1.1 What is scientific evidence?
	4.1.2 Complementary therapies
	4.1.3 Alternative therapies
	4.2 Why do some people with cancer choose CAM?
	4.3 What types of CAM are there?
	4.4 Important safety information
	4.5 What should I ask my doctor about CAM?
	4.6 How do I decide?
	4.7 Costs
	4.8 Finding a complementary therapist
	4.8.1 Professional associations
	4.9 Talking to complementary therapists
5. Impact of cancer and treatment on my life	5.1 Family
	5.2 Work
	5.2.1 Taking time off work
	5.2.2 Financial issues
	5.3 Education/Studies
	5.4 Partner relationships
	5.5 Social life
	5.6 Body image and sexuality
	5.7 Diet
	5.7.1 Coping with eating problems and side effects
	5.7.2 How to gain weight
	5.7.3 Access to a dietitian
	5.7.4 Recipes and snacks
	5.8 Exercise
6. What support is available?	6.1 Emotional support
	6.2 Accommodation
	6.3 Practical support
	6.4 Transport/parking
	6.5 Financial assistance
	6.6 Support for the family
	6.7 Access to wigs
7. Where can I get further information?	7.1 Websites
	7.2 Telephone helplines
	7.3 Clinical cancer nurse
8. Discussion Forum	8. Discussion Forum

#### Development of software

Development of the technical aspects of the web-based tool was undertaken by the Distributed Computing Research Group, University of Newcastle, Australia. Established web design principles [44,45] were employed to ensure that the tool allows the user to extract the desired information as easily as possible. The site is hosted on a secure Apache Tomcat server at the University of Newcastle. A security certificate protects the site and access to the site is via secure HTTP (HTTPS). The site has been written using HTML5, facilitating the provision of multimedia content and reducing the need for special software on participant computers. Some server behaviour was achieved using code written in Java or PHP. Modules adapted from public domain content management (CMS) software have been used to facilitate generation and modification of textual content. Video content uses the capabilities of HTML5. A mySQL database installed on the web server securely stores user-identified audit information that can be later collated.

#### Functionality

The information presented in the web-based intervention tool will be tailored to the circumstances of the individual. Participants will only be able to view information that is relevant to their own specific diagnosis and the treatment options that their treating doctor has nominated as suitable for them. Some therapeutic options may be medically contraindicated due to the patient’s health or age at diagnosis. Tailoring to the needs of individuals is further exemplified with information presented in multiple formats, including short videos, text and images to suit different learning styles and literacy levels of participants. Expandable text is provided for sections of information which may be of a sensitive or potentially distressing nature to enable participants to exercise more control over the type of information they wish to view (refer to Figure 1). In addition, explicit categorisation strategies are used to improve recall and understanding, with each section of information summarised into key points.

**Figure 1 Fig1:**
[figure not shown]
Screenshot of Expandable Text Section.

Participants will be able to search for desired information using the topic tabs, expandable side menus and search function. If participants have additional questions or concerns about any information contained within the web-based intervention, an icon is available at the bottom of every page, which allows the participants to send their questions to the study nurse via automated email (refer to Figure 2). Participants are also able to ask questions and connect with other participants in the intervention group via a discussion forum. Participants are able to create threads on the discussion forum and comment on other users’ threads. The discussion forum is monitored by the lead clinical researcher.

**Figure 2 Fig2:**
[figure not shown]
Screenshot of Information Icon.

In order to ensure the acceptability and usefulness of the information intervention, a feedback mechanism has been integrated into the web software. Participants in the intervention group will be asked to indicate whether they found the information on the web page they are viewing useful. This data will be collected via a pop-up window and will occur randomly, up to a maximum of 4 times per user. The custom built software will collate data on each user’s access behaviour and feedback.

#### Pilot testing

The penultimate version of the web-based information intervention was pilot tested with a sample of haematological cancer patients (n = 33). Pilot participants were asked to rate sections of information and complete a brief survey about the acceptability of the intervention. Feedback obtained from consumers was evaluated and incorporated if recommended changes reflected the views of the majority. Members of the expert advisory groups were consulted during this revision process to ensure the accuracy of amended information.

### Intervention delivery

#### Web-based information tool

Participants in the intervention group will gain access to the web-based information intervention at the time of recruitment. For consenting patients, the treating doctor will log in to the administrative interface of the intervention website and complete a brief online form indicating the patient’s name, date of birth, gender, diagnosis, and the treatment options that are relevant to the patients’ circumstances (see Figure 3). Using this information the web-based intervention will automatically generate a user ID for the patient. This user ID will be provided to both the patient and their Support Person along with detailed instructions on how to access the web-based information tool both in hospital and at home. The information entered into the online form by the clinician will also be used to tailor the content of the web program.

**Figure 3 Fig3:**
[figure not shown]
Screenshot of Administrative Interface.

At least two study iPads (touch screen tablet devices) will be provided to each hospital for use by inpatients who have been assigned to the intervention group to access the web-based information intervention. Outpatients without internet access will also be able to use the iPads to access the intervention while visiting the hospital for outpatient appointments. Support Persons will be able to use the iPads when at hospital, and access the web-based tool using their home internet access. Use of the web-based information intervention will be self-guided, with no restriction placed on how and to what extent it is used. At the time of recruitment, intervention patients will be provided with a demonstration, to supplement the written instructions, on how to use the iPad and access the web-based intervention by a research nurse or study volunteer.

#### Nurse-delivered telephone support

Intervention patients and Support Persons will also have access to an experienced haematological cancer nurse. Participants can contact the cancer nurse via a toll free telephone number to seek information or ask questions. Participants will also have the option of contacting the nurse via the information icon in the web-based information tool, as described above. An automated email will be sent to the nurse providing the patient’s first name, the user’s relationship to the patient, the topic of the page where the icon was clicked, the question/query indicated by the user, the contact telephone number indicated by the user, and details of the treating doctor. The cancer nurse will have experience with addressing information needs and adjustment issues and will be supervised by the lead clinical researcher (WS).

### Usual care

Patients and Support Persons randomised to the control group will receive usual care. The control condition reflects the usual process of psychosocial support and information provision for newly diagnosed haematological cancer patients and their Support Persons. While usual care may vary slightly between participating hospitals and clinicians, psychosocial care and information provision in this early phase of cancer survivorship usually involves the provision of generic written material provided by healthcare providers and non-government patient support organisations such as Cancer Council and/or Leukaemia Foundation. Participants in the control group may seek and obtain information or support that is available on the Internet or from other sources, but will not have access to the web-based intervention or nurse-delivered telephone support specifically developed for this trial.

### Data collection

Outcome data will be collected from patients and Support Persons via paper-and-pen surveys at 2, 4, 8 and 12 weeks post-recruitment (refer to Figure 4). These time points were chosen given the intervention primarily targets the provision of care at diagnosis and during treatment, and it is during this time period when patients are making decisions about and receiving intensive treatment. Data collection for participants who are in hospital will be conducted by research nurses or study volunteers, depending on the preference and policy of the individual hospital. All research nurses and study volunteers will receive comprehensive training. The research nurse or study volunteer will visit the participant in hospital to provide them with the survey package appropriate to the time point and answer any questions about survey completion. Survey packages will be provided to the participant in an unsealed envelope, allowing them to seal their responses prior to returning the survey to the research nurse or volunteer. Participants who do not wish to complete the survey are able to seal the envelope and return it uncompleted. For participants who are not in hospital, including all Support Persons, surveys will be sent via mail with a reply paid envelope to allow return of the completed survey. The study co-ordinator at each participating hospital will be requested to keep an up-to-date record of participants who are discharged or deceased in order to arrange the appropriate method of data collection or remove them from the contact list respectively.

**Figure 4 Fig4:**
[figure not shown]
Flowchart of study design.

A reminder phone call will be made to non-responders approximately two weeks after the time of the initial delivery of each survey. Reminder phone calls will only occur for participants who are not in hospital. For non-responders who are in hospital, the research nurse or study volunteer will prompt the participant to either complete the survey if they wish to do so or return it uncompleted.

### Outcome measures

Patients and Support Persons in both the intervention and control groups will complete self-report measures of unmet needs, anxiety and depression at 2, 4, 8 and 12 weeks post-recruitment.

#### Patient outcomes

Unmet needs will be assessed using the health systems and information domain of the Supportive Care Needs Survey - Short Form (SCNS-SF34) [46]. The SCNS-SF34 assesses unmet needs across five domains: (i) psychological; (ii) health systems and information; (iii) patient care and support; (iv) physical and daily living; and (v) sexuality. Participants indicate their level of need for each item using a five point scale: ‘no need, not applicable; ‘no need, satisfied’; ‘low need’; ‘moderate need’; and ‘high need’. Domain scores are calculated by summing item responses within the domain. The SCNS-SF34 has high internal consistency for each of the five factors (Cronbach alpha’s 0.86 to 0.96) and good convergent validity [46].

Anxiety and depression will be assessed using the Hospital Anxiety and Depression Scale (HADS) [47]. The HADS is a 14-item self-report instrument which measures anxiety (7 items) and depression (7 items) within the last seven days. Participants respond to each item on a four point scale with 3 indicating that the symptom is severe or frequent, and 0 indicating the symptom is absent or almost absent. Scores from items are summed to provide an overall score out of 21 for the anxiety and depression subscales. The HADS has acceptable internal consistency, construct validity, and discriminant validity [48].

#### Support person outcomes

Unmet needs for Support Persons will be assessed using the information and relationships domain of the Support Persons Unmet Needs Survey (SPUNS) [49], which is a 78-item measure of unmet needs across 6 domains: (i) Information and relationships; (ii) Emotional needs; (iii) Personal needs; (iv) Work and finance; (v) Healthcare access and continuity; and (vi) Worries about the future. Participants provide responses for each item on a five point likert scale from ‘no unmet need’ to 4 ‘very high unmet need’. Domain scores are calculated by summing item responses and dividing by the number of non-missing responses within the domain. The SPUNS has high acceptability, item test-retest reliability, internal consistency (Cronbach alpha = 0.99), and face, content, and construct validity [49].

Anxiety and depression will be measured using the Depression and Stress Scale-21 (DASS-21) [50], a 21-item self-report instrument which measures depression (7 items), anxiety (7 items) and stress (7 items). Participants respond to each item using a four point scale from ‘Did not apply to me at all’ to ‘Applied to me very much or most of the time’. Scores on each scale (Depression, Anxiety, and Stress) are calculated by summing item responses within the scale and multiplying totals by two. Reliability, convergent validity and discriminant validity of the total score and three sub-scales of the DASS-21 is adequate [51,52].

#### Demographic characteristics

Demographic characteristics including date of birth, gender, postcode, marital status, education, time since diagnosis, distance to the cancer centre (for patients only) and relationship to the patient (for Support Persons only) will be collected via participant self-report two weeks post-recruitment.

#### Process measures

Psychological support service utilisation will be examined at 12 weeks post-recruitment for patients and Support Persons in both the intervention and control group. Participants will be asked whether and how many times they have accessed psychological support from a range of services in the past 12 weeks.

Process and acceptability measures (intervention group only): For intervention patients and Support Persons use of the program will be monitored via embedded web monitoring tools. Data collected will include the number of times a participant accesses the web-based intervention, and the type of information accessed will be recorded by the website. Use of the 1800 number will also be monitored via a call log. Acceptability and usefulness of the web-based intervention will be examined via a series of questions in the Week 4 survey for intervention group participants. Clinicians will complete a brief assessment of the perceived acceptability of the intervention at the end of the recruitment period.

### Sample size

Patient sample: Assuming a 75% consent rate, 450 patients will be approached to give a sample of 340 at baseline. Allowing for 15% attrition, at each follow up, a sample of 145 per group will be available at 4 weeks, 123 per group at 8 weeks and 105 per group at 12 weeks. Assuming 90% power and 5% significance level this will enable detection of differences between groups of, 0.38 standard deviations (SD) at 4 weeks, 0.41 SD at 8 weeks and 0.45 SD at 12 weeks follow up. There are over 400 patients diagnosed each year in NSW with the cancers specified in our eligibility criteria. High volume centres will be targeted for recruitment. Current studies being conducted by the group involving clinic-based recruitment are achieving an 85% consent rate. These effect sizes are clinically relevant.

Support person sample: For each of the 340 patient participants, one Support Person will be recruited. It is anticipated that 80% of patients will have a Support Person who provides data at 4 weeks. Allowing for 15% attrition at each follow up, a sample of 115 per group will be available for comparison at 4 weeks, 100 per group at 8 weeks and 85 per group at 12 weeks. Assuming 90% power and 5% significance level this will enable detection of differences between groups of 0.4 SD at 4 week follow up and 0.45 SD at 8 weeks and 0.5 SD follow up. These effect sizes are clinically relevant.

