### Aims

This study will examine, using a randomised controlled trial, whether an integrated approach that includes access to a web-based information tool and nurse-delivered telephone support reduces for both haematological cancer patients and their Support Persons (i) unmet information needs (primary outcome); and (ii) depression; and (iii) anxiety (secondary outcomes); at 2, 4, 8 and 12 weeks follow up.

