### Hypotheses

It is hypothesised that:(i)Patients who are allocated to the intervention group will have a 0.45 standard deviation lower mean total score on the Health System and Information Needs Domain of the Supportive Care Needs Survey Short Form (SCNS-SF34) (primary outcome), and 0.45 standard deviation lower anxiety and depression scores as measured by the Hospital Anxiety and Depression Scale (HADS) (secondary outcomes), compared to patients who are allocated to the control condition;(ii)Support Persons who are allocated to the intervention group will have a 0.45 standard deviation lower unmet information needs score as measured by the Support Persons Unmet Needs Survey (SPUNS) (primary outcome), and a 0.45 standard deviation lower depression and anxiety score as measured by the Depression and Stress Scale-21 (DASS) (secondary outcomes), compared to Support Persons who are allocated to the control condition.

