## Method

### Study design

This study is a non-blinded, parallel-group, multi-centre randomised controlled trial comparing the effectiveness of a web-based information tool and nurse-delivered telephone support with usual care. The primary outcomes for both patients and Support Persons are unmet information needs and the secondary outcomes are anxiety and depression. All outcomes are assessed a 2, 4, 8 and 12 weeks post-recruitment. This study is funded by a Cancer Institute New South Wales Translation Program Grant (10/THS/2-14).

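### The patient attrition rule, the four-visit schedule and the stated sample sizes cannot all hold; the rule as written gives 89 per group and about 85% power for 0.45 SD at week 12

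*Protocol article*

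**What the plan says.** The Sample size section (patient sample) starts from consent. "Assuming a 75% consent rate", it says, "450 patients will be approached to give a sample of 340 at baseline". With equal groups that is 170 per group.

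The attrition rule and the first size come together: "Allowing for 15% attrition, at each follow up, a sample of 145 per group will be available at 4 weeks". The later sizes are "123 per group at 8 weeks and 105 per group at 12 weeks". The section then gives the differences detectable with 90% power at the 5% level: 0.38 SD at week 4, 0.41 SD at week 8 and 0.45 SD at week 12. It gives no number and no detectable difference for week 2.

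Elsewhere week 2 is an outcome visit like the others. The Aims set the outcomes "at 2, 4, 8 and 12 weeks follow up". Study design says "All outcomes are assessed a 2, 4, 8 and 12 weeks post-recruitment", and Data collection says "Outcome data will be collected from patients and Support Persons via paper-and-pen surveys at 2, 4, 8 and 12 weeks post-recruitment".

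The Hypotheses section gives the expected patient effect: "Patients who are allocated to the intervention group will have a 0.45 standard deviation lower mean total score". It attaches no time point to the 0.45 SD.

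**The concern.** A loss of 15% at every follow-up, over four follow-ups, is four successive reductions. The listed sizes contain three, the first of which lands on week 4. One of three things must give: the rule, the count of follow-ups, or the sizes.

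The stated power at the last visit depends on which one. The 0.45 SD detectable at week 12 equals the effect in the Hypotheses, and 105 per group is almost exactly the number that 90% power requires. With no margin at that visit, one more 15% step takes power below the stated level. The Statistical analysis section compares groups at each time point and makes complete case analysis primary, so the number retained at each visit matters directly.

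**Working it through.** **Inputs.** From Sample size: 340 patients at baseline, so 170 per group (450 × 0.75 = 337.5, which confirms that 340 is the consent yield); 15% attrition; 90% power; 5% significance level. From Aims, Study design and Data collection: follow-ups at weeks 2, 4, 8 and 12. From Hypotheses: 0.45 SD. The protocol does not say whether the test is one- or two-sided. I take two-sided, because it reproduces the stated figures; one-sided would give 94.7% power with 105 per group at 0.45 SD.

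**Step 1: reproduce the stated sizes.** Number per group after k losses = 170 × 0.85^k.

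- k = 1: 144.5 (stated 145 at week 4)
- k = 2: 122.8 (stated 123 at week 8)
- k = 3: 104.4 (stated 105 at week 12)

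The sizes follow from three losses, with k = 1 placed at week 4.

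**Step 2: reproduce the stated power.** For two equal groups of n and a standardised difference d, power ≈ Φ(d × √(n/2) − 1.96).

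- n = 145, d = 0.38: 89.9%
- n = 123, d = 0.41: 89.5%
- n = 105, d = 0.45: 90.3% (two-sample t: 90.1%)

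So the protocol's method is a simple two-group comparison at each visit, and its power figures are right for the sizes it lists.

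**Step 3: apply the rule at all four follow-ups.** A fourth step gives 170 × 0.85^4 = 88.7, about 89. The difference detectable with 90% power is approximately (1.96 + 1.2816) × √(2/n); the table uses the two-sample t version, which differs by at most 0.003 SD.

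| Week | Stated n per group | n under the rule | Stated detectable difference | Detectable difference under the rule | Power for 0.45 SD under the rule |
|---|---|---|---|---|---|
| 2 | none | 145 | none | 0.38 | 97% |
| 4 | 145 | 123 | 0.38 | 0.415 | 94% |
| 8 | 123 | 104 | 0.41 | 0.45 | 90% |
| 12 | 105 | 89 | 0.45 | 0.49 | 85% |

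The week-12 power is 84.7% by the two-sample t and 85.1% by the normal approximation. The week-8 power is 89.8% and 90.1% respectively.

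**Step 4: what the listed sizes imply if they are kept.** From 170 to 145 is 25 lost per group, 25/170 = 14.7%, over the whole period from recruitment to week 4. After that the loss is about 15% from week 4 to 8 and again from week 8 to 12. Cumulative loss by week 12 is 1 − 105/170 = 38%, against 1 − 89/170 = 48% under the four-step rule.

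**The case against.** The strongest reply is that week 2 serves as the baseline. The analysis model includes baseline data, no survey before week 2 is described, and demographics are collected at week 2. The Support Person paragraph also gives its sizes from week 4 onwards. Weeks 4, 8 and 12 would then be three follow-ups, and 145, 123 and 105 would follow from the rule. This makes it plausible that the sizes, and not the wording of the rule, are what was intended, and that part stands. It does not remove the inconsistency. The Aims call week 2 a follow-up, Intervention delivery starts web access at recruitment, and 340 is the number expected to consent, not the number expected to return a week-2 survey.

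A second reply is that attrition rates are planning assumptions and the listed sizes are explicit. That is fair: at those sizes the power is correct, so the fault is not in the power calculation. But the rule is explicit too, and the protocol gives no reason to prefer one over the other.

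A third reply is that the planned mixed model uses all visits and may gain precision. It may. The sample size calculation takes no credit for it, however, and takes no account either of allocation by week, which could act in the other direction. The 85% is comparable with the protocol's own 90%; neither is the power of the final model.

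A reader might also infer that the plan assumes no loss before week 2. The text does not say so. It is silent on week 2, and the 25 per group it allows to be lost by week 4 could all be lost before the week-2 survey. For the same reason the missing week-2 size does little harm in itself: if patients lost do not return, the week-2 number is at least the week-4 number.

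**Conclusion.** The point holds as an internal inconsistency: 15% at each follow-up, four follow-ups, and 145/123/105 at weeks 4, 8 and 12 cannot all be true. Under the rule as written, week 12 has 89 per group, power for 0.45 SD is about 85% (5 points below the stated figure), and the difference detectable with 90% power is 0.49 SD. The stated detectable differences at weeks 4 and 8 also move, from 0.38 to 0.415 SD and from 0.41 to 0.45 SD.

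This rests on 170 per group at recruitment, a two-sided 5% test, and a simple comparison at each visit as in the protocol.

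Two stronger conclusions are tempting and not supported. One is that 105 is simply wrong and 89 right; that follows only if the rule, and not the list of sizes, is what was intended. The other is that the trial lacks 90% power for its primary hypothesis. The Hypotheses section names no time point for 0.45 SD, and even under the four-step rule power is about 97%, 94% and 90% at weeks 2, 4 and 8. The shortfall is confined to week 12.

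**What to change.** Decide which statement was intended and make the other agree with it.

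- **If the rule stands:** restate the patient sizes as 145, 123, 104 and 89 per group at weeks 2, 4, 8 and 12, with detectable differences of about 0.38, 0.415, 0.45 and 0.49 SD. Give power for 0.45 SD at week 12 as about 85%, noting that this is a simple comparison at that visit.
- **If the sizes stand:** keep 145, 123 and 105 with their detectable differences. Reword the attrition assumption as 15% in total from recruitment to week 4 and 15% in each later interval, and give the expected number at week 2.

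Either way, say how week 2 is counted in the attrition chain. The cost is a text correction. The first option makes the stated week-12 power slightly less favourable. Neither option needs extra patients.

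### Support Person sample size: 115 per group at 4 weeks detects about 0.43 SD at 90% power, not the stated 0.4 SD, and the 12-week 0.5 SD does not match the hypothesised 0.45 SD

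*Protocol article*

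**What the plan says.** All the sizing figures are in the Sample size section of the protocol article, in the Support Person paragraph.

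- Base: "For each of the 340 patient participants, one Support Person will be recruited".
- Availability: "It is anticipated that 80% of patients will have a Support Person who provides data at 4 weeks".
- Sizes: "Allowing for 15% attrition at each follow up, a sample of 115 per group will be available for comparison at 4 weeks", followed by "100 per group at 8 weeks and 85 per group at 12 weeks".
- Detectable differences: "Assuming 90% power and 5% significance level this will enable detection of differences between groups of 0.4 SD at 4 week follow up", then 0.45 SD at 8 weeks and 0.5 SD for a last follow-up. That last value carries no visit label and is read here as 12 weeks.

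The Hypotheses section, item (ii), states the expected effect: "Support Persons who are allocated to the intervention group will have a 0.45 standard deviation lower unmet information needs score". It names no visit. The Aims list 2, 4, 8 and 12 weeks, and the Statistical analysis section compares the groups at each time point.

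**The concern.** Support Person unmet information need is one of the trial's two named primary outcomes, so this paragraph supports a primary comparison. Two things in it do not fit.

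- The 4-week detectable difference is smaller than 115 per group can deliver at the stated power.
- The effect in hypothesis (ii), 0.45 SD, is smaller than the 0.5 SD that the plan gives for 12 weeks. The two sections therefore differ on what the 12-week Support Person comparison is sized for.

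At stake is how the results are read. Someone weighing a null 4-week result against the stated 90% power for 0.4 SD would credit the trial with more sensitivity than it has. A reader who carries the hypothesised 0.45 SD to 12 weeks would do the same there.

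**Working it through.** **Inputs.** Power 90%, significance 5%, and the per-group sizes and detectable differences are from the Sample size section. The 0.45 SD is from hypothesis (ii). Sidedness is not stated; two-sided is assumed and tested below.

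**Formula.** For two groups of n with SD = 1, detectable difference = (z₀.₉₇₅ + z₀.₉₀) × √(2/n) = (1.960 + 1.2816) × √(2/n) = 3.2416 × √(2/n).

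**Step 1: reproduce the patient figures.**

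| n per group | Computed | Stated |
|---|---|---|
| 145 | 0.381 | 0.38 |
| 123 | 0.413 | 0.41 |
| 105 | 0.447 | 0.45 |

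All three reproduce to two decimals. One-sided 5% would give 0.344, 0.373 and 0.404, which do not. The plan's method is therefore recoverable, and it is two-sided.

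**Step 2: apply the same method to Support Persons.**

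| Visit | n per group | Computed, normal (t) | Stated |
|---|---|---|---|
| 4 weeks | 115 | 3.2416 × √(2/115) = 0.428 (0.429) | 0.4 |
| 8 weeks | 100 | 3.2416 × √(2/100) = 0.458 (0.461) | 0.45 |
| 12 weeks | 85 | 3.2416 × √(2/85) = 0.497 (0.500) | 0.5 |

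The 12-week value reproduces, the 8-week value is slightly favourable, and the 4-week value does not reproduce.

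**Step 3: size of the 4-week error.** Power for 0.4 SD at 115 per group is Φ(0.4/√(2/115) − 1.960) = Φ(1.073) = 85.8% (t: 85.6%). The n needed for 90% is 2 × 3.2416² / 0.4² = 131.4, so 132 (133 by t).

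**Step 4: power for the hypothesised 0.45 SD**, from Φ(0.45/√(2/n) − 1.960).

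- 115 per group: Φ(1.452) = 92.7% (t: 92.5%)
- 100 per group: Φ(1.222) = 88.9% (t: 88.6%)
- 85 per group: Φ(0.974) = 83.5% (t: 83.1%)

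Ninety per cent power for 0.45 SD needs 2 × 3.2416² / 0.45² = 103.8, so 104 per group.

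**Step 5: the 80%.** There are 340/2 = 170 patients per group.

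- Applied to all patients, with loss to 4 weeks already included: 0.80 × 170 = 136 per group, detecting 0.39 SD. A further 15% loss at each later visit gives 115.6 and 98.3, so 116 and 98, detecting 0.43 and 0.46 SD.
- Applied to patients retained at 4 weeks: 0.80 × 145 = 116 per group, detecting 0.43 SD. Applying 15% attrition to the 136 gives the same: 136 × 0.85 = 115.6.

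The stated 115 follows from the second reading. On that reading too, 0.4 SD is not reached.

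**The case against.** **Rounding.** 0.43 becomes 0.4 at one decimal. But one decimal would also turn the 8-week 0.46 into 0.5, and the plan prints 0.45. Rounding to the nearest 0.05 would turn 0.428 into 0.45. Rounding down to a multiple of 0.05 would give the printed set from the t values, but rounding a detectable difference down overstates what the sample can do. The patient figures have two decimals.

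**One-sided testing.** For 115, 100 and 85 per group this gives 0.386, 0.414 and 0.449. It does not produce the Support Person set, and it breaks the patient figures.

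**Small consequence.** This stands. Power for 0.4 SD falls from 90% to about 86%, and for the hypothesised 0.45 SD the 4-week power exceeds 90%.

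**The 12-week limit is disclosed.** This also stands. The plan prints 0.5 SD for the last visit, the figure is right, and hypothesis (ii) names no visit. A reader might infer a hidden shortfall, but the document does not claim 90% power for 0.45 SD in Support Persons at 12 weeks. What remains is a mismatch between two sections.

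**Stronger readings that do not hold.** A reader might infer that 115 contradicts the 80% assumption, because 80% of 340 gives 136 per group and 136 would detect about 0.4 SD. The text does not say that the 80% is of all 340, and 115 follows if it applies to patients retained at 4 weeks. That the authors took 0.4 SD from 136 per group would be a guess. A reader might also object that 15% attrition from 115 gives 98 and 83, not 100 and 85. The printed sizes are round numbers, and the effect is negligible: 0.465 against 0.461 SD, and 0.506 against 0.500 SD (t).

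**Conclusion.** The concern holds in limited form. The 4-week Support Person figure is wrong as written: 115 per group detects about 0.43 SD at 90% power, and power for 0.4 SD is about 86%. The 8-week figure is marginally favourable. The 12-week figure is correct but does not line up with the 0.45 SD of hypothesis (ii), for which power is about 83%. The meaning of the 80% is an ambiguity, not a proven contradiction.

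This rests on a two-sided 5% test, equal groups, independent observations and a simple comparison of two means. The document does not state these, but the patient figures reproduce on that basis. The normal and t calculations agree to within half a percentage point of power.

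**What to change.** In the Support Person paragraph of the Sample size section:

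- Restate the detectable differences at 90% power, two-sided 5%, as 0.43, 0.46 and 0.50 SD for 115, 100 and 85 per group, and label the last one as 12 weeks.
- Add that power for the hypothesised 0.45 SD is about 93%, 89% and 83% at 4, 8 and 12 weeks. This reconciles the paragraph with hypothesis (ii).
- Say whether the 80% is of all 340 patients or of those retained at 4 weeks. If it is of all 340, with loss to 4 weeks included, the sizes also change, to 136, 116 and 98 per group, detecting 0.39, 0.43 and 0.46 SD.

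The cost is an edit to the text and, if the printed sizes stand, a slightly less favourable figure at 4 and 8 weeks. Recruitment, design and analysis do not change.
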